### Unmet need

Although recommended in the guidelines, significant weight loss and remission of type 2 diabetes through calorie restriction is not commonly used in routine care.^6^ A major reason for this is the challenge of achieving and maintaining weight loss over time without intensive and long-term support from care providers, who have limited resources. eHealth can offer an effective and potentially more patient-friendly approach than face-to-face meetings, as it is less time-consuming than standard care for both the patient and the healthcare provider. In a randomised trial, we aim to investigate the clinical effectiveness and cost-effectiveness of achieving diabetes remission through calorie restriction with a specially developed eHealth programme compared with face-to-face meetings. The comparison group in this study receives an intervention identical to the intervention in the DiRECT study, as this intervention, which is based on face-to-face counselling, has been shown to be effective. The intervention group in this study participates in a similar programme, but the support is provided via an eHealth platform.

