### Objective

Our primary hypothesis is that eHealth support is non-inferior to face-to-face support in helping patients with type 2 diabetes achieve remission through calorie restriction. Our secondary hypothesis is that eHealth support will be more cost-effective than face-to-face support.

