For the cost-effectiveness analysis, the incremental costs per QALYs gained is the main outcome. Costs include the total diet replacement portions used, meetings with the study team including travel time, time taken by the study team to assess and provide feedback on participants’ measurements each week, other healthcare visits and hospital days, blood glucose-lowering and blood pressure-lowering medications, costs of HbA1c analyses and scales, blood pressure monitors and blood glucose metres. Participants will answer the SF-36 and EQ-5D-5L questionnaires to analyse how they experience their health and quality of life. Costs are analysed based on the intention-to-treat principle. Mean costs are calculated for each group, with cluster-adjusted standard errors for each cost item. Incremental costs per QALY after 2 years are given as the difference in total costs of the groups after 2 years divided by the difference in QALYs. The cost per QALY gained is compared with the Swedish threshold of SEK 500 000. If the ratio is below the threshold, the intervention is categorised as cost-effective. If both interventions are cost-effective, the most effective one is recommended for introduction into normal healthcare.

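### The cost-effectiveness decision rule sets no condition on the sign of the QALY difference and cannot classify both arms, so as written it can recommend the wrong programme

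*Protocol article*

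**What the plan says.** All of the relevant text is in the cost-effectiveness paragraph of the protocol article, Statistical analyses.

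- Main economic outcome: "For the cost-effectiveness analysis, the incremental costs per QALYs gained is the main outcome".
- Definition of the ratio at two years: "the difference in total costs of the groups after 2 years divided by the difference in QALYs".
- Comparison: "The cost per QALY gained is compared with the Swedish threshold of SEK" 500 000.
- First decision: "If the ratio is below the threshold, the intervention is categorised as cost-effective".
- Second decision: "If both interventions are cost-effective, the most effective one is recommended for introduction into normal healthcare".

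The paragraph does not say which group is subtracted from which, what happens if the QALY difference is negative or zero, or how a negative ratio is read. Under Unmet need, the intervention group is the eHealth arm: "The intervention group in this study participates in a similar programme, but the support is provided via an eHealth platform". The trial has two arms, both active, and no usual-care arm (Trial design and setting; Strengths and limitations).

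**The concern.** A cost-effectiveness ratio has its usual meaning only when the arm being judged gains QALYs. If that arm saves money and loses QALYs, the ratio is a saving per QALY given up, and a large value is favourable. If it costs more and loses QALYs, the ratio is negative, so it lies below any positive threshold although the arm is worse on both counts. A rule that looks only at whether the ratio is below SEK 500 000 treats all these cases alike.

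The second decision adds a separate difficulty. It presupposes a verdict on each arm, while the plan defines one comparison between the arms. It then chooses on effect, with no reference to what the extra effect costs.

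At stake are the second stated hypothesis, "Our secondary hypothesis is that eHealth support will be more cost-effective than face-to-face support", and the recommendation for routine care. The design makes the problem region plausible. The primary aim is non-inferiority ("Our primary hypothesis is that eHealth support is non-inferior to face-to-face support"), and eHealth has 11 scheduled video meetings against 33 face-to-face meetings, so cheaper eHealth with similar QALYs is a result the trial could well produce.

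**Working it through.** **Inputs.** The threshold L = SEK 500 000 per QALY is from the protocol article. It is a policy figure, so there is nothing to reproduce. The protocol gives no cost or QALY values, so those below are illustrative assumptions.

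**Notation.** dC and dQ are the cost and QALY differences, eHealth minus face-to-face. The written rule calls eHealth cost-effective if dC/dQ < L. The reference is incremental net monetary benefit, INMB = L × dQ − dC, with eHealth preferred if INMB > 0.

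**Step 1: when the two agree.**
- If dQ > 0, multiplying dC/dQ < L by dQ gives dC < L × dQ, that is INMB > 0. The rule is right.
- If dQ < 0, the same multiplication turns the inequality round: dC > L × dQ, that is INMB < 0. The rule is reversed, whatever the sign of dC.
- If dQ = 0, the ratio is undefined and no verdict follows.

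**Step 2: worked cases.**

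| dC (SEK) | dQ | dC/dQ | Written rule, eHealth | INMB = 500 000 × dQ − dC |
|---|---|---|---|---|
| −10 000 | −0.005 | 2 000 000 | not cost-effective | −2 500 + 10 000 = +7 500 |
| −1 000 | −0.02 | 50 000 | cost-effective | −10 000 + 1 000 = −9 000 |
| +5 000 | −0.01 | −500 000 | cost-effective | −5 000 − 5 000 = −10 000 (dominated) |
| −20 000 | +0.02 | −1 000 000 | cost-effective | +10 000 + 20 000 = +30 000 |

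The first three verdicts are wrong. The fourth, with a QALY gain, is right.

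**Step 3: direction of subtraction.** Reversing the order in both differences changes both signs and leaves the ratio unchanged. The number alone therefore does not show which arm gains QALYs or which arm the verdict concerns. That has to be stated.

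**Step 4: the sentence about both interventions.** Two arms give one incremental ratio. Separate verdicts would need each arm compared with no programme, which the trial does not observe. Suppose such figures were brought in from outside (assumed):
- eHealth: SEK 30 000 for 0.10 QALY = 300 000 per QALY; net benefit 50 000 − 30 000 = 20 000.
- Face-to-face: SEK 50 000 for 0.11 QALY = 454 545 per QALY; net benefit 55 000 − 50 000 = 5 000.

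Both pass and the rule recommends face-to-face. Its extra 0.01 QALY costs 20 000 / 0.01 = SEK 2 000 000 per QALY, four times the threshold, and its net benefit is SEK 15 000 lower.

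**Step 5: how easily the sign can fall either way.** With 106 participants, 53 per arm, and an assumed two-year QALY SD of 0.2 to 0.4, the standard error of dQ is SD × √(2/53) = 0.04 to 0.08. If true QALYs were equal, half of all estimates would show a QALY loss for eHealth. This is conditional on that assumption and is not a forecast.

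**The case against.** The strongest defence rests on the word gained. The main outcome and the comparison with the threshold are both phrased as cost per QALY gained, and such a ratio exists only for the arm that gains QALYs. In the first worked case, face-to-face gains 0.005 QALY for SEK 10 000 more, which is 2 000 000 per QALY, and it is correctly found not cost-effective. In the third case eHealth gains no QALYs, so it has no such ratio to classify. This stands: on that reading the threshold sentence is sound. The text does not adopt it explicitly, though, because the operative definition is a plain quotient of group differences and the verdict attaches to the intervention, a term used elsewhere for eHealth.

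That reading also does not rescue the final sentence, since only one arm is then judged. One might instead apply the same ratio to both arms, so that they pass or fail together. Below the threshold, choosing the more effective arm is then correct. Above it neither arm is recommended, even when cheaper eHealth has positive net benefit. In neither case has each arm been shown to be cost-effective.

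It is also fair to say that the two faults do not simply add up. If separate verdicts cannot be formed, the choice on effect never comes into play. If they can be formed, it applies only when both arms pass. Face-to-face would therefore not be recommended on every chance QALY advantage.

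A reader might infer that eHealth is most likely to fall where the rule fails. The documents do not support that. They forecast neither costs nor QALYs, the Introduction allows that eHealth may be more effective, and eHealth carries costs of its own: weekly staff review, home devices and HbA1c tests every second month. If eHealth gains QALYs, even the literal rule is right.

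**Conclusion.** The decision rule is not valid as written. Read literally for eHealth, it is reversed for every negative QALY difference and gives no verdict at zero. Read for the arm that gains QALYs, its first part is correct, but that reading has to be stated. On any reading, one ratio between two active arms cannot establish that both are cost-effective, and a choice on effect alone can select an arm whose extra QALYs cost more than SEK 500 000 each.

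The reversal is algebra and depends on no assumed value. The monetary sizes (for example +7 500 rejected, −10 000 accepted) are illustrations, because the protocol gives no cost or QALY figures.

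A reader might also infer that the QALY difference will be left unadjusted for baseline utility. The article does not say how that difference is estimated, and such detail may properly sit in an analysis plan, so it is no part of this point. Nor does the point touch the primary HbA1c comparison. The economic outcomes are secondary, are assessed at 24 months and are to be published separately (Secondary outcomes; Publication plan). The matter is of moderate weight: it should be corrected before the economic analysis, because an analysis plan that follows the article would inherit the rule.

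**What to change.** In the cost-effectiveness paragraph, and in the analysis plan if it repeats the rule:

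1. Define both differences as eHealth minus face-to-face.
2. Base the decision on incremental net monetary benefit, 500 000 × QALY difference − cost difference, and prefer eHealth if it is above 0.
3. Report the ratio only where it can be interpreted, naming the arm that gains QALYs; where one arm is cheaper and at least as effective, say so instead of giving a ratio.
4. Replace the final sentence with a recommendation of the arm with the higher net benefit.

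The cost is a few sentences and no new data. Recruitment in Jönköping began in November 2023, so its 24-month data could not have existed when the article appeared in July 2025. If the analysis plan already uses net benefit, the article's wording only needs to be brought into line with it.

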## Ethics and dissemination

The eDIT was approved by the Swedish Ethical Review Authority (Dnr 2022-02242-01) on 10 May 2022. All participants give written informed consent before participating in the study. This study is conducted on the basis of the Declaration of Helsinki and in accordance with Good Clinical Practise. The sponsor of the study is Umeå University. The two principal investigators, JO and AS, have access to the final data set and will conduct the analyses together with other researchers and research students. The results will be published in peer-reviewed journals by the principal investigators together with other researchers who fulfil the four author criteria of the International Committee of Medical Journal Editors.^32^ In addition, the results are presented at national and international scientific conferences and discussed at joint meetings with patient organisations. Participant-level data cannot be made publicly available due to legal regulations but may be obtained from the principal investigator on reasonable request.
